### Plans to promote participant retention and complete follow-up {18b}

Patients are allowed to withdraw study participation at any time and for any reason. However, as interventions are only applied when the patient is under general anesthesia and most study data are collected within the first 24 h after CPB while the patient is being either under general anesthesia or shortly after awakening from an open chest cardiac surgery procedure, withdrawal rate taking together with the dropout rate (see {14}) and missing data is thought to be less than 10% of the cases during the whole study period.

In order to reduce the risk of loss to follow-up during phone surveys up to 6 months post-surgery, at least one phone number of a close relative is recorded at the time of recruitment.

### Data management {19}

After inclusion, every patient receives an individual paper CRF, which is filled out as the study proceeds individually. These CRFs are stored at a central place up to postoperative day 8 for assessors who visit patients up to postoperative day 7. From then onwards, CRFs are stored in numerical order in a secure place with restricted access. Every quartile of the total sample size, which is after 35, 70, 105, and 140 patients, paper CRFs will be digitalized and copies will be saved on at least 2 external disks. For consequent data analysis, we deem single data entry appropriate in this monocentric study.

All EIT and echocardiographic files will be copied from the specific devices on a monthly basis with copies again saved on at least 2 external disks. Final data storage will be in locked cabinets with restricted access.

Paper CRFs will be stored in a secure place at least 10 years after study close-out, whereas original patient files are digitalized after hospital discharge and will be retained indefinitely as all digitalized study data are.

### Confidentiality {27}

After trial enrolment, every patient receives a pseudonym consisting of letters and serial numbers. From then onwards, personal as well as study-related data will only be collected under this pseudonym in the patient’s individual paper CRF. The list of personal patient data linked to the specific pseudonym will be locked in a separate cabinet with access only by the principal investigator.

Echocardiographic data will be anonymized before data analysis and EIT data will be saved under the corresponding pseudonym (see additional file 1, page 9). For phone surveys after 1 and 6 months, the assessor will receive a list with the patient names including date of birth for a correct identification. However, obtained data of these surveys will again be collected in the corresponding pseudonymized CRF (see Additional file 1, page 14).

In general, all study-related information will be stored securely at the study site and any personal patient information will be either locked in cabinets with limited access or will be only accessible via specific user names and passwords in digital databases.

### Plans for collection, laboratory evaluation, and storage of biological specimens for genetic or molecular analysis in this trial/future use {33}

Aliquots of plasma probes will be labeled with the corresponding pseudonym/time point of collection and stored at -80 °C in the laboratories of the Department for Anesthesiology, BG University Hospital Bergmannsheil, until the final publication of the main and ancillary studies. Eventually, not all of these aliquots will be utilized for evaluation. At this time, no further analysis of this plasma biobank is planned. If future ideas for evaluation might evolve which are not yet specified in the current version of the study protocol, a new positive votum of the local REC as well as additional participant approval must be obtained before analysis (see {26b}).

## Statistical methods

### Statistical methods for primary and secondary outcomes {20a}

The intervention group (perioperative individualized FCV) will be compared with best clinical practice PCV as the control group for all primary analyses. The primary study endpoint will be assessed with a linear regression model using the intervention group as an independent variable and the EuroSCORE II as an additional covariable. For all continuous secondary endpoints, similar linear regression models will be fitted. All binary secondary outcomes will be calculated using a logistic regression model as well as SIRS-free days using a Poisson regression model with the same independent variables. For the analyses of multiple secondary outcomes, the Bonferroni method for appropriate adjustment of the overall significance will be utilized.

For all confirmative statistical analyses, 2-sided *p*-values with a significance level of 0.05 will be utilized. *P*-values will be reported to four decimal places with *p*-values less than 0.001 reported as *p* < 0.001. All analyses will be conducted with the statistical software R (www.r-project.org, version ≥ 4.1.0).

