#### Important secondary outcomes of the main study

Oxygenation indices at different perioperative time points (Table 1, “art BGA”)Plasma IL-8 concentrations at different perioperative time points (Table 1)Perioperative ventilation pressures (mean and peak airway pressure, driving pressure), C_dyn_, airway resistances, and mechanical power of ventilation [26] up to 24 h after termination of CPBWeaning times from mechanical ventilationIncidence of postoperative pneumonias with the need of antibiotic treatment during the complete inpatient stay (suspected and/or confirmed, see below)Incidence of postoperative pulmonary complications (PPCs) during the first seven postoperative days including compound outcome analysis and single PPC analysis. PPCs encompass (modified from [20])New invasive ventilationNon-invasive ventilationPost-extubation respiratory acidosis (pH ≤ 7.3 and PaCO2 > 45 mmHg)ReintubationReadmission to ICU due to pulmonary reasonsMild hypoxemia defined as an PaO2/FiO2 < 300 but ≥ 200Moderate hypoxemia defined as an PaO2/FiO2 < 200 but ≥ 100Severe hypoxemia defined as an PaO2/FiO2 < 100Acute respiratory distress syndrome (ARDS) according to the Berlin criteria [27]Implantation of a veno-venous ECMOSuspected pneumonia defined as new pulmonary infiltrates plus 2 or more of the following clinical parameters: temperature > 38.5 or < 35.5°C, leucocyte count > 12 or < 4/nl and purulent secretions including antibiotic treatmentConfirmed pneumonia defined as pulmonary infiltrates and microbiological germ proof of tracheal aspirationsBronchoscopyPleural drainage due to pleural effusionsPleural drainage due to pneumothoraxIncidence of postoperative extra-pulmonary complications (PEPCs) during the first seven postoperative days including compound outcome and single PEPCs analysis. As PEPCs the following items are definedSepsis and septic shock (as defined in [28])Postoperative coronary interventionPostoperative wound infection with the need for antibiotic treatmentOther sites of infection with the need for antibiotic treatmentPericardial tamponade or other bleeding with intervention such as re-sternotomyImplantation of any device for extracorporeal life support (ECMO, Impella) or intra-aortic balloon pumpNon-pulmonary ICU readmissionAcute kidney injury with a Kidney Disease: Improving Global Outcomes (KDIGO) stage 2 or 3 [29]Postoperative delirium diagnosed by the Confusion Assessment Method for the ICU (CAM-ICU) [30]Systemic inflammatory response syndrome (SIRS) (according to [28]) free days during the first seven postoperative daysLengths of intensive/intermediate care unit stays and time to dischargeHospital readmission and mortality rate after one and 6 months post-surgery (Table 1, phone surveys)

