#### Outcome parameters for ancillary studies

Sub-study on cardiovascular-ventilation interactions (n≥40/group)Perioperative echocardiographic evaluation of pulmonary circulation and right ventricular function parameters at three different times, (1) preoperative TTE before induction of anesthesia (baseline), (2) TEE 1 before CPB, and (3) TEE 2 30 to 60 min after CPB (Table 1). Parameters include [31]iPulmonary acceleration time and estimated pulmonary artery pressures during ins- and expirationiiRight ventricular index of myocardial performance (RIMP)iiiTricuspid annulus velocity S’ivTricuspid annular plane systolic excursion (TAPSE)vRight ventricular outflow tract fractional shortening (RVOT FS)viFractional area change (FAC)viiLongitudinal strain analyses by speckle tracking echocardiography.For explorative analyses, final values of each right function parameter
at the defined times as well as the relative changes from baseline to
intraoperative data and relative changes between pre- and post-CPB measurements
will be assessed.Serum concentrations of CK-MB and high-sensitivity troponin up to postoperative day 5 (Table 1)Plasmatic brain natriuretic peptide (BNP) concentrations and relative changes from baseline (i.e. before induction of general anesthesia) up to postoperative day 5 (Table 1)Central venous oxygen saturations at 8 perioperative time points up to 24 h after CPB (venous BGA, Table 1)Perioperative catecholamine concentrations up to 24 h after CPB (Table 1)Sub-study on perioperative lung aeration parameters based on electrical impedance tomography (EIT) data (n≥50/group)Parameters include [32]iGlobal inhomogeneity indexiiCenter of ventilationiiiRegional ventilation delayivSurface of ventilated areavDorsal fraction of ventilated area [33].

EIT recordings are performed at 6 perioperative times: (1) patient breathing spontaneously in supine position before induction of general anesthesia (baseline), (2) after individualization of preoperative, group-specific ventilation, (3) after postoperative ICU admission and re-individualization of group-specific ventilation, (4) on pressure support ventilation with a PEEP of 5–6 cm H_2_O and support pressure of 6 cm H_2_O during weaning from mechanical ventilation, (5) 30–60 min after extubation, (6) 24 h after CPB end (Table 1). The explorative analyses will include final values of each parameter as well as relative changes from baseline, i.e., the spontaneously breathing patient preoperatively.

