**Table 1 Tab1:**
[figure not shown]
Time schedule for enrolment, allocation, interventions and assessments in the main and ancillary studies. Calculations for the Assess Respiratory Risk in Surgical Patients in Catalonia (ARISCAT) Score [34] can only be completed when SpO_2_ is measured at the time of patient arrival in the induction room. The EuroSCORE II [35] is recalculated after CPB based on the actual intraoperative cardiac surgical interventions. Additional arterial BGAs are conducted simultaneously to the EIT recordings on CPAP and pressure support ventilation during weaning as well as 30–60 min after extubation. Close-out of participants is after the second phone survey 6 months after the cardiac surgery procedure. The first phone survey is conducted one month postoperatively. Post-allocation time points: Base, patient breathing spontaneously before induction of anesthesia; T−2, after group-specific individualization of ventilation and before skin incision; T−1, 15 min after thoracotomy; T0, after CPB termination and transfusion stop from the extracorporeal circulation; T1–24, appropriate hour after CPB end. BGA, blood gas analysis; BNP, brain natriuretic peptide; CK-MB, creatine kinase MB; CPAP, continuous positive airway pressure ventilation during weaning; PEEP, positive end-expiratory pressure; PEPCs, postoperative extra-pulmonary complications; POD, postoperative day; PPCs, postoperative pulmonary complications

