## Discussion

During on-pump cardiac surgery procedures, lungs do not only need to withstand mid-term invasive ventilation in deep general anesthesia, surgical manipulations, and recurrent phases of apnea with consecutive atelectasis formation and atelectrauma. Lungs also receive a further hit by partial ischemia and reperfusion through the use of CPB, resulting in LIRI. These various injuries and their combination induce a pulmonary and systemic hyperinflammatory state [8, 37] which to a large extent accounts for the common postoperative pulmonary dysfunctions [10]. Clinical studies in the setting of cardiac surgery could demonstrate a reduction of key inflammatory biomarkers when lung protective ventilation strategies with respect to an open-lung approach [22] and combined with low tidal volumes [21] were applied perioperatively. However, the recent multicenter study PROVECS could not show a clinical benefit towards PPCs prevention when comparing a perioperative, generalized open-lung concept with common practice ventilation in cardiac anesthesia [9].

The trial scope of FLOWVENTIN HEARTSURG is to evaluate the new ventilatory mode of FCV in a single center RCT of a medium sample size in a perioperative approach. We did not exclude any preexisting patient comorbidities per se, except for situations with an initially modified (hyper-) inflammatory environment like in acute myocardial infarction and preexisting pneumonia as well as (suspicion of) endocarditis or intake of any preoperative immunosuppressive medication. The same open approach was chosen for the surgery: All types of single and combined surgical procedures with the exception of heart transplantation and assist device implantations are allowed as on-pump interventions. The reasoning behind this was to have a really thorough sample of cardiac surgical patients and procedures as the basis for our study. However, statistical analysis will adequately account for preoperative comorbidities and the severity of surgery as the EuroSCORE II will function as an additional covariable that specifically weighs patient-, cardiac-, and operation-related factors in the analysis of primary and secondary endpoints.

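### The primary model adjusts for EuroSCORE II without naming the version, and the score is recalculated after bypass; the covariate should be the preoperative value, with pre-ventilation IL-8 added if it was sampled

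*Protocol article*

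**What the plan says.** Section {20a} defines the primary analysis as a linear regression on arm "and the EuroSCORE II as an additional covariable". It names no other covariate. Continuous secondary endpoints get similar linear models; binary outcomes (logistic) and SIRS-free days (Poisson) use the same independent variables. Whatever EuroSCORE II means in the primary model, it therefore means throughout.

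The only sentence on how the score is obtained is in the Table 1 legend: "The EuroSCORE II [35] is recalculated after CPB based on the actual intraoperative cardiac surgical interventions". The Discussion gives its purpose. It is to account for preoperative comorbidities and the severity of surgery, because "the EuroSCORE II will function as an additional covariable that specifically weighs patient-, cardiac-, and operation-related factors".

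The primary outcome ({12}) is the final IL-8 value 6 h after the end of CPB. The secondary outcomes include "Plasma IL-8 concentrations at different perioperative time points (Table 1"). The Table 1 legend defines a time point called Base, before induction of anaesthesia. The body of Table 1 is not shown, so the readable text does not tie IL-8 to Base.

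**The concern.** A score that is recalculated must also have an earlier value, so each patient has two candidate covariates. One reflects the planned operation. The other reflects the operation performed, and is fixed after allocation and after exposure to the allocated ventilation, under care providers who are not blinded ({17a}). The model names neither. The Discussion's reference to severity of surgery makes the recalculated value a natural reading.

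Adjusting for a post-randomisation variable is safe only if treatment does not affect it. If treatment does affect it, part of the treatment effect is removed or distorted. An unnamed version also leaves a choice that could still be made once outcome data are visible.

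A separate, lesser point is precision. The endpoint is a single final value and the trial is sized at 80% power with almost no reserve. A patient's own IL-8 before ventilation, if measured, is a natural covariate and is not in the model.

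**Working it through.** **1. Which EuroSCORE II?** The order of events in the article is:

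- Assignment is made before the procedure, once the operating slot is confirmed ({16b}).
- Group-specific ventilation is individualised before skin incision (time T−2, Table 1 legend).
- EuroSCORE II "is recalculated after CPB based on the actual intraoperative cardiac surgical interventions" (Table 1 legend).
- IL-8 is measured 6 h after the end of CPB ({12}).

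The recalculated value therefore comes after randomisation and after the start of the intervention. The value for the planned procedure does not depend on treatment. Sections {20a} and the Discussion fit either one.

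**2. Size of a possible bias.** With a covariate shifted by treatment, the bias in the arm coefficient is approximately

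bias = −(slope of outcome on score) × (between-arm shift in score caused by treatment), all in SD units.

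The article gives neither input, so both are assumptions: slope 0.1 to 0.3, shift 0 to 0.2 SD.

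- Shift 0: bias 0, whatever the slope.
- Slope 0.1, shift 0.1: 0.01 SD; 0.01/0.5 = 2% of the planned effect.
- Slope 0.2, shift 0.1: 0.02 SD; 4%.
- Slope 0.3, shift 0.2: 0.06 SD; 12%.

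**3. The plan's own sample size.** Section {14} gives d = 0.5, two-sided α = 0.05, power 0.80 and a two-sample t-test, resulting in 2 × 64 = 128. With noncentrality d√(n/2):

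- 64 per arm: 0.5 × √32 = 2.828, 126 degrees of freedom, power 0.8015. The stated 128 reproduces.
- After the planned loss: 140 × 0.9 = 126, or 63 per arm. 0.5 × √31.5 = 2.806, 124 degrees of freedom, power 0.7952.

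The calculation takes no credit for any covariate, so omitting baseline IL-8 does not make it wrong.

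**4. What a pre-ventilation IL-8 term could add.** With partial correlation r between that value and IL-8 at 6 h, residual variance is multiplied by 1 − r² and the effective effect size is 0.5/√(1 − r²). At 63 per arm, with one degree of freedom fewer:

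| r (assumed) | 1 − r² | Effective d | Power |
|---|---|---|---|
| no baseline term | 1.00 | 0.500 | 79.5% |
| 0.1 | 0.99 | 0.503 | 79.9% |
| 0.2 | 0.96 | 0.510 | 81.1% |
| 0.3 | 0.91 | 0.524 | 83.1% |
| 0.4 | 0.84 | 0.546 | 86.0% |
| 0.5 | 0.75 | 0.577 | 89.5% |

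Because EuroSCORE II is already in the model, r is the correlation left after adjusting for it, and d = 0.5 is taken relative to the SD left after it. The article gives no value for r.

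**The case against.** The best reply on EuroSCORE II is that ventilation mode has no evident route to changing which operation is done. That is mainly a surgical decision, and section {20c} argues similarly about surgical complications. Patients with a second CPB run are excluded from analysis ({20c}), which removes some of the cases where the operation could depart most from plan. This stands, and it is why the bias is put as probably small. It does not settle which value enters the model.

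A reader might infer that the plan does use the post-bypass score. The documents do not say so: recalculation implies a preoperative value as well, and the Discussion's wording fits both. The defect is an unnamed version.

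On IL-8, a reader might infer that the trial already holds a baseline value and is discarding free power. That is not supported either. The article links a pre-induction baseline explicitly to BNP, EIT and echocardiography, but nowhere in the readable text to IL-8. Section {18a} describes one aliquot per participant assayed for the primary endpoint, and {33} says not all aliquots will be used, so a stored sample is not necessarily an assayed one. Elective patients without pneumonia, endocarditis or immunosuppression may also have pre-induction IL-8 that predicts the post-bypass level poorly. Comparing randomised final values remains valid without it.

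A reader might also fault the EIT and echocardiography sub-studies for relying on relative change. For EIT the plan states: "The explorative analyses will include final values of each parameter as well as relative changes from baseline". The echocardiography text likewise plans both, and these analyses are exploratory. No criticism is made there.

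**Conclusion.** The point holds as a correction that should be made, in two parts of unequal strength.

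The firm part is that the EuroSCORE II version is not specified, and one of the two available values is fixed after randomisation and after ventilation began. This affects the primary and all secondary models. The expected bias is small: zero if ventilation mode leaves the operation unchanged, and 0.01 to 0.06 SD under the assumed non-zero slopes and shifts. The case for acting is that the risk can be removed for nothing.

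The conditional part is baseline IL-8. It is a matter of efficiency, not bias, and applies only if a sample was taken before group-specific ventilation. A Base sample would qualify: it follows allocation but precedes induction, so treatment cannot have affected it. The gain ranges from negligible (0.4 percentage points at r = 0.1) to about 10 points at r = 0.5, and nothing in the article says where in that range this trial lies.

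**What to change.** Before unblinding of the analysts, record that:

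- the covariate in every primary and secondary model is the EuroSCORE II calculated before surgery for the planned procedure;
- the recalculated EuroSCORE II is used only to describe the cohort;
- if Table 1 schedules IL-8 at Base, or at another time before group-specific ventilation, that value is added to the primary model on the same scale as the outcome. If there is no such sample, no baseline term is added.

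The first two changes cost only wording, since the preoperative score is implied by the recalculation. The third costs one degree of freedom and, where a stored sample has not been assayed, some ELISA work. The sample size need not change.

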#### Key secondary objectives of the main study

To determine whether FCV compared to PCV benefits the perioperative lung function with respect to oxygenation and decarboxylation capacities, the incidence of PPCs and postoperative extra-pulmonary complications (PEPCs), weaning times from mechanical ventilation and duration of intensive/intermediate care unit stays and time to discharge.

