### Sample size {14}

The sample size was calculated according to the study hypothesis. Based on the previous results of protective ventilation protocols in the setting of on-pump cardiac surgery [21, 22], the effect size of the intervention on postoperative plasmatic IL-8 concentrations was estimated as moderate being well aware about the exploratory nature of this study of mid-term clinical FCV utilization. Under these assumptions (Cohen’s d = 0.5), the total sample size required to achieve a power of 1-β = 0.8 for a two-sample *t*-test at a two-sided level α = 0.05 resulted in 2*64 = 128 [36]. As the primary endpoint is obtained 6 h after termination of CPB, most dropouts will be due to a second cardiopulmonary bypass phase within this time frame or other in {11d} defined stop criteria in estimated 10% or less of the cases. Therefore, an additional 10% of patients will be randomized summing up to a total sample size of 128*1.1 = 140.8 ≈ 140 randomized study participants.

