### Methods in analysis to handle protocol non-adherence and any statistical methods to handle missing data {20c}

In this first larger trial of mid-term FCV application in high-risk cardiac surgery procedures, more than one cardiopulmonary bypass time, intraoperative death, and/or cardiopulmonary resuscitation which are exclusively due to major intraoperative surgical complications as well as study protocol deviations with respect to the allocated intervention for more than 5 min (see {11d}) are defined as stop criteria. It is almost impossible that the perioperative ventilatory mode has an impact on the etiology of these stop criteria, especially as lungs are not being ventilated during CPB in the current study protocol. However, major surgical complications leading to the defined stop criteria and the incidence of the criteria itself significantly affect postoperative patient outcomes. Thus, these patients will be excluded from data analysis whereas all other participant data will be analyzed “as randomized” following an intention-to-treat analysis.

Due to the nature of the intervention and the collection of predominantly short-term data, there will be very few missing data regarding secondary outcomes and (nearly) no missing data with respect to the primary endpoint. Since in most cases these will be due to operational disturbances, loss of paper CRFs, and laboratory errors, missing data can be assumed to be completely missing at random. As the omitting of the (few) missing values will not lead to bias this approach will be utilized for this trial.

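### SIRS-free days, a count that cannot exceed 7, are given a plain Poisson model whose standard errors may be wrong in either direction; secondarily, linear regression of durations favours the arm with more in-hospital deaths

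*Protocol article*

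**What the plan says.** Section {20a} of the protocol article assigns one model to each type of outcome. The primary endpoint is regressed linearly on group and EuroSCORE II. For the rest: "For all continuous secondary endpoints, similar linear regression models will be fitted". Binary outcomes get logistic regression. The remaining outcome is handled as "SIRS-free days using a Poisson regression model with the same independent variables". Multiplicity is covered in one clause: "the Bonferroni method for appropriate adjustment of the overall significance will be utilized".

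Section {12} defines SIRS-free days over the first seven days after surgery, so a patient can score only 0 to 7. It also lists weaning times, length of ICU or intermediate-care stay and time to discharge. The key secondary objectives in section {7} repeat these durations, for example "weaning times from mechanical ventilation". No time-to-event model is named for any of them. They are neither binary nor the SIRS count, so they come under the linear rule.

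On who is analysed, section {20c} removes patients who meet a stop criterion, including intraoperative death due exclusively to surgical complications: "Thus, these patients will be excluded from data analysis whereas all other participant data will be analyzed “as randomized” following an intention-to-treat analysis". Other missing values are taken to be missing completely at random: "As the omitting of the (few) missing values will not lead to bias this approach will be utilized for this trial". Mortality at one and six months is a secondary outcome, so deaths after surgery are foreseen, and those patients stay in the analysis set.

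**The concern.** A Poisson model takes its standard error from the assumption that variance equals mean. A count with a ceiling of 7 has no reason to obey this. If most patients sit near 7, the variance is far below the mean, the standard error is too large, and a real effect can be missed. If some patients have SIRS on most days and others on none, the variance exceeds the mean, the standard error is too small, and chance differences look significant. Bonferroni does not help, because it lowers the threshold but uses the same p-values.

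For the durations, linear regression reads a shorter time as a better one. A patient who dies on the ward leaves hospital early in the data. If the value is instead dropped, the comparison is among survivors, and death is plainly not a random laboratory or paperwork loss. At stake are outcomes that the article presents as relevant to patients: the abstract names SIRS-free days and stays, and section {7} names the durations.

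**Working it through.** **The plan's own figure.** Section {14} states: "Under these assumptions (Cohen’s d = 0.5), the total sample size required to achieve a power of 1-β = 0.8", and then "two-sample *t*-test at a two-sided level α = 0.05 resulted in 2*64 = 128". The normal approximation gives n = 2(1.960 + 0.842)²/0.5² = 62.8, or 63 per arm. The noncentral t gives 63.77, or 64 per arm and 128 in total, with power 0.801. The figure is reproduced. It rests on IL-8 alone and does not change. I use 64 per arm below.

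**SIRS-free days.**

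Inputs from the article: range 0 to 7, Poisson model, two-sided 5%. Assumed, because the article gives no distribution: a beta-binomial count with mean 7p and within-patient correlation ρ between days.

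- Variance/mean: v = (1 − p)(1 + 6ρ).
- Poisson standard error divided by the true one: 1/√v.
- Actual type I error at nominal 5%: about 2Φ(−1.96/√v).

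| Mean | ρ | v | SE ratio | Type I error |
|---|---|---|---|---|
| 6 | 0.3 | (1/7)(2.8) = 0.40 | 1.58 | 0.2% |
| 5 | 0.3 | (2/7)(2.8) = 0.80 | 1.12 | 3% |
| 4.5 | 0.3 | (2.5/7)(2.8) = 1.00 | 1.00 | 5% |
| 4 | 0.3 | (3/7)(2.8) = 1.20 | 0.91 | 7% |
| 3 | 0.3 | (4/7)(2.8) = 1.60 | 0.79 | 12% |
| 4 | 0.7 | (3/7)(5.2) = 2.23 | 0.67 | 19% |

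Simulation with 20,000 runs, 64 per arm, no effect and no covariate gave 0.25%, 12.3% and 19.0% in the (6, 0.3), (3, 0.3) and (4, 0.7) rows. Robust standard errors in the same three rows gave 4.7 to 5.0%. A wider grid (means 2 to 6, ρ from 0 to 0.7, 3,000 runs per cell) put the Poisson error between about 0% and 30%. The robust error stayed between 3.9% and 5.6% in every cell, including runs in which 3% of patients died and were scored 0.

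**Durations.**

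The article gives no mortality and no stay distribution, so all of this is assumed.

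*Hand calculation.* If survivors stay 12 days on average and a death occurs on day 2, k excess deaths shift that arm's mean by −k(12 − 2)/64. That is −0.16 day for one and −0.47 day for three.

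*Simulation.* The latent stay is log-normal (median 11 days, log-SD 0.5) and identical in both arms. Sicker patients die more often, on days 1 to 7. Differences in mean stay, in days:

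| Mortality | Death ends the stay | Deaths omitted |
|---|---|---|
| 2% vs 2% | 0 | 0 |
| 3% vs 2% | −0.17 | −0.09 |
| 5% vs 2% | −0.49 | −0.26 |
| 8% vs 2% | −0.96 | −0.51 |

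Both treatments favour the arm with more deaths; omission roughly halves the bias.

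*Scale against noise.* A log-normal stay with mean 12 and log-SD 0.5, 0.7 or 0.9 has SD 12√(exp(σ²) − 1) = 6.4, 9.5 or 13.4 days. The standard error of the difference is SD × √(2/64) = 1.1, 1.7 or 2.4 days. Three excess deaths (0.47 day) therefore move the estimate by about 0.4, 0.3 or 0.2 standard errors.

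**The case against.** Four points can be made for the plan.

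First, how a death enters each endpoint is the kind of detail that an article leaves to the full protocol or the SAP. This stands: the absence of a scoring rule is not itself the fault. But the article does name the models, and a plain Poisson for a count capped at 7 and a linear model for time to discharge are choices, not gaps.

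Second, section {20c} attributes missing data mostly to disturbances, lost forms and laboratory errors. It does not say that deaths are treated as missing, and it already removes some intraoperative deaths. This also stands, so omission is only one possible handling. The other, entering the observed short stay, gives the larger bias on the assumed figures.

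Third, the Poisson error is close to nominal in the middle of the grid. With no SIRS-day distribution in the documents, neither its direction nor its size is known. That is right, and it is why the point is that the standard errors may be wrong, not that they are wrong by a known amount.

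Fourth, mean differences in days are a legitimate target, and mortality will be reported alongside.

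A reader might go further and infer that skewed durations make linear regression invalid. The check does not support this: with log-normal durations at 64 per arm the type I error was 4.0 to 4.7%. What is lost is power, for example 60% on the raw scale against 79% on the log scale at log-SD 1.0, and the assumed shape favours the log scale. A reader might also infer that mortality could reverse the sign of the effect on stay. The documents give no mortality to support that, and even three excess deaths move the estimate by under half a standard error, so only an already negligible difference could change sign.

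**Conclusion.** The point holds for secondary outcomes. The Poisson model for SIRS-free days has correct standard errors only if variance happens to equal mean. Under the assumed beta-binomial distributions, the nominal 5% test runs from about 0.2% to 19% over the tabulated cells and passes through 5% in between. The data will decide which applies, and a plan should not depend on that.

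The point on durations is weaker. Linear regression would tilt the comparison towards the arm with more in-hospital deaths. The tilt is about 0.16 day per excess death if survivors average 12 days, death falls on day 2 and the death enters at its observed length. It is smaller if deaths are omitted, and zero at equal mortality. It would not arise if a worst value were assigned to deaths, but the article names no such rule.

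The primary IL-8 analysis and the 128 evaluable patients are not affected.

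**What to change.** For SIRS-free days, keep the covariates (group and EuroSCORE II) and either use robust (sandwich) standard errors with the Poisson model, or replace it by a quasi-binomial model out of 7 or a proportional-odds model. State in advance the score given to a patient who dies within the seven days.

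For weaning time, ICU or intermediate-care stay and hospital stay, analyse time to successful extubation and time to discharge alive, with death as a competing event (cause-specific hazards or a Fine-Gray model) and EuroSCORE II as covariate.

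This changes analysis wording only, before the data set is fixed, and needs no new data or patients. The cost is interpretability: except where the Poisson model is kept with robust errors, effects become hazard or odds ratios instead of differences in days or ratios of mean counts. Report medians or mean differences descriptively beside them, together with deaths by arm.
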